# Form for Registered and Unregistered Medicines *(Refer Question B19)*

## Information required for trials involving administration of medicines currently registered in New Zealand

**This form is be completed for all medicines including non-registered medicines except where the medicine will be given regardless of entry into the trial (eg, anaesthetic) and that medicine is not being studied in any way**

| Trade name of medicines |  |
| --- | --- |
|  | |
| Generic name of medicines |  |
|  | |
| Pharmacological class |  |
|  | |
| Form of administration used in the study |  |
|  | |
| Recommended dose range |  |
|  | |
| Contraindications |  |
|  | |
| Known or possible interactions with non-trial medicines the participants may be taking |  |
|  | |
| Common side effects and serious adverse reactions |  |
|  | |
| Additional information, eg, long half-life, immunosuppression |  |
|  | |

**Appendix 1.**

***Research Study Design continued (from section A.3.1)***

**Phase 1 – details of exercise intervention**

The exercise interventions will be based on previously successful protocols, undertaking in the exercise physiology laboratory. In phase one, 60 participants will be randomly assigned to LIET (low intensity exercise) (N = 20), MVIT (maximal volitional intensive training) (N=20) or high intensity training (N = 20). All subjects will undergo a standardised, supervised paired maximal intensity exercise treadmill test to measure VO2max and paired blood tests, before and immediately after the 12 week intervention. The exercise intervention will be undertaken in groups of around 6 participants per group.

The three exercise prescriptions will be isocaloric ie the same overall energy expenditure will take place per session in all three groups but the method, hence time requirements to achieve this will vary. All groups will complete 3 supervised training sessions per week, based in Hagley Park. Exercise groups will be instructed by health and physical activity undergraduates from CPIT, Canterbury or Lincoln University who will all have current First Aid qualifications and will be given training and guidance on how to organise and conduct the training sessions. All participants will exercise with the aid of a heart rate monitor, thereby allowing the participants to control their corresponding exercise heart rate relative to VO2peak. The instructors will monitor each participant’s heart rate during exercise to ensure training sessions are carried out in the desired heart rate throughout the 12 week training period. As fitness improves, the exercise load ie intensity of exercise will be increased.

**High intensity exercise groups (HIITT and MVIT).** The HIIT and MVIT groups will complete a warm-up for 5 min (at an intensity of 50-60% VO2peak or 65-75% heart rate peak). The HIIT group will then walk for four intervals of 4 min at 80-90% VO2peak (85-95% heart rate peak), interspersed with 3 recovery periods of 3 min at 50-60% VO2peak. The MVIT group will exercise ‘as hard as they can’ ie at a similar intensity to the final minute of the exercise treadmill test undertaken at baseline, for 60 second intervals, followed by a cool down period then further maximal intensity exercise over the course of the session. At the end of the session, HIIT and MVIT subjects will complete a cool-down of 3 min at 50-60% VO2peak.

**Low intensity exercise group.** The LIET group will complete walking at an intensity of 50-60% for the time it will take to burn off similar calories to the HIIT and MVIT groups. (The approximate value will be ~41 min which follows previous research paradigms (Rognmo *et al*, 2004) and is based on the average VO2peak for all groups measured at baseline).

**Phase 2**

In phase two, results from phase one will be used to fine-tune the testing and training protocols. In this phase 44 new to the study participants will be randomly assigned into 2 groups; the best high intensity programme from Phase (ie HIIT or MVIT) and a control group undertaking LIET. There will be 22 participants in each group. Subjects will undertake blood testing and VO2 max as for Phase one at times 0, 13 and 26 weeks. The second VO2max test done at 13 weeks will be used to check progress and adjust the training intensities for the final 3 months of training. Once a week each exercise group will come together at a local venue (Halswell Health Medical Centre or the Whanau Tautoko Charitable Trust) where instructors (trained undergraduates from CPIT, Canterbury or Lincoln University who will all have current First Aid qualifications) will take the group through their training for that day. The other two exercise sessions each week will take place at a venue chosen by the individual participants, either at the participant’s home or in a convenient community location. All participants will exercise with the aid of a heart rate monitor thereby allowing the participants to control their corresponding exercise heart rate relative to VO2peak. The instructors will monitor each participant’s heart rate each week to ensure training sessions are carried out in the desired heart rate throughout the 6 month training period

See next page for the testing protocols.

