
#### A4. Participants

| A4.1 How many participants do you intend to recruit? (Include details for each locality organisation.) | |
| --- | --- |
|  | Phase 1;- 60 participants, anticipating that 48 will complete the study (16 in each arm).  Phase 2;- This less structured community based phase of the study is likely to experience a higher ‘drop out’ rate. 60 participants will be recruited, anticipating that 44 participants will complete the study (22 in each arm). |
|  | |
| A4.2 Give a justification for the number of research participants proposed, giving the details of power calculations when appropriate. | |
|  | A sample size of 16 in each group for the first study, will enable effect sizes >1.0 to be detected as statistically significant (two tailed-alpha=0.05) with 80% power. Assuming an untrained VO2 max of 30 ± 4ml/kg/min, this equates to differences in changes in VO2 max over 12 weeks of approximately 4 ml/kg/min.  A sample size of 22 per group in the second study will enable effect sizes >0.9 to be detected as statistically significant (two tailed-alpha=0.05) with 80% power, this equates to differences in changes in VO2max over 26 weeks of approximately 3.5ml/kg/min.  (To place this in context, a sedentary individual typically has a VO2 max of 25-35ml/kg/min +/- SD of 4 and a trained adult has a VO2 max around 40-60 ml/kg/min). |
|  | |
| A4.3 If randomisation is used, explain how this will be done. | |
|  | After consenting and baseline measurements, subjects will be randomly allocated in a 1:1:1 ratio to the exercise interventions, under the supervision of the medical biostatistician (CF).For both studies it is important to achieve a balance in gender and this will be achieved by stratified randomisation. |
|  | |

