#### Relevance and responsiveness to Māori

| F2. **All health research conducted in Aotearoa New Zealand is of relevance to Māori**. How relevant is a decision to be made by Māori. The researcher must be able to articulate the context and the relevance of the proposed research to Māori and the possible consequences for Māori health outcomes, and generally, the greater the degree of relevance to Māori, the greater the expectation of participation of Māori and hence consultation expectations. | | | |
| --- | --- | --- | --- |
| F2.1 Given your approach to sampling, what are the anticipated numbers of Māori participants? | | | Phase 1 (efficacy study). This phase will be offered to the general population of Christchurch and will not specifically target Maori. Previous research would suggest that, using this general approach, Maori participation will be around 5% ie 3 of 60.  Phase 2 (effectiveness study). Sampling for this longer duration study will be focussed on and within the Maori community, in partnership with Maori Health workers. We are aiming for 50% of the participants being of Maori ethnicity (22 of 44 participants). |
|  | | | |
| F2.2 What is the incidence among Māori of the health issue/disability relevant to the study? | | | Modelling of incidence of type 2 diabetes would suggest that rates in Maori are around x3 those of the general population. Prevalence of one or more features of the metabolic syndrome is >80%, after age 40 years (*Simmons, Diabetes Care, 2004*). |
|  | | | |
| F3. Please explain how this research will contribute to improving Māori health outcomes and reducing health inequalities for Māori. | | | |
|  | Maori have a high prevalence of diabetes and an excess burden of diabetes related morbidity and mortality. Community based lifestyle programmes aimed at reducing this burden are already underway in Christchurch and elsewhere in New Zealand. Knowing what the optimal exercise prescription is for maximising fitness and management of metabolic risk factors, will inform both Maori and non Maori health professionals about the best exercise prescription to incorporate into their lifestyle programmes. | | |
|  | | | |

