## Details of proposed research study

| Title of research project: | Health Benefits of high intensity exercise for populations at risk of diabetes and CVD |
| --- | --- |
|  | |
| Name of research director/investigator: | [name] |
|  | |
| Location/s of proposed study: | Christchurch Diabetes Centre, [name] University of Canterbury Dovedale Campus. |
|  | |
| Number of participants: | 104 |
|  | |
| Organisations providing support (in money or kind) for the direct and indirect costs of the research *(please provide names of organisations and details of the type of support provided)*: | HRC District Health Board Research Fund will reimburse a portion of staff time, assay costs and overheads. |
|  | |
| Relationship of proposed research to the pharmaceutical industry or other company involved in health research *(please describe the involvement of industry in your proposed research and provide details of support to be received from them)*: | No relationships |

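### Phase 2: A4.1 recruits 60 to end with 44 completers, but Appendix 1 randomises only 44, leaving no allowance for dropout behind the 22 per group on which the power statement rests

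*Protocol*

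**What the plan says.** Section A4.1 plans Phase 2 with an attrition allowance. It gives the reason, "This less structured community based phase of the study is likely to experience a higher ‘drop out’ rate", and then the numbers: "60 participants will be recruited, anticipating that 44 participants will complete the study (22 in each arm"). Section A4.2 builds the power statement on the completer number: "A sample size of 22 per group in the second study will enable effect sizes >0.9 to be detected as statistically significant", two-sided at 0.05, "with 80% power, this equates to differences in changes in VO2max over 26 weeks of approximately 3.5ml/kg/min".

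Appendix 1, under Phase 2, gives 44 as the number allocated: "In this phase 44 new to the study participants will be randomly assigned into 2 groups", followed by "There will be 22 participants in each group".

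Two other places use 44 for Phase 2. Form A gives "Number of participants: | 104", which is 60 + 44. Section F2.1 says "We are aiming for 50% of the participants being of Maori ethnicity (22 of 44 participants"), although its Phase 1 line uses the recruited number (3 of 60).

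For Phase 1 the protocol is consistent. A4.1 recruits 60 and expects 48 to complete, and Appendix 1 randomises 60, 20 to each arm.

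**The concern.** The same number cannot be both those randomised and those who finish unless nobody leaves, and A4.1 says that people will leave. Appendix 1 is the detailed design text that study staff would turn to when setting up allocation. If it is followed, enrolment stops at 44 and the margin that A4.1 built in disappears, in the longer phase and with two of the three weekly sessions unsupervised (B1). The primary comparison of change in VO2max would then rest on fewer than the 22 per group that A4.2 assumes. The ethics committee is also shown two study sizes, because recruits over both phases total 120 under A4.1 and Form A declares 104.

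**Working it through.** **Inputs.** From A4.1: Phase 2, 60 recruited and 44 completing (22 per arm); Phase 1, 60 recruited and 48 completing. From A4.2: 22 per group, effect size 0.9, difference about 3.5 ml/kg/min, SD 4, two-sided alpha 0.05, power 80%. From Appendix 1: 44 randomised in Phase 2, 22 per group.

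**Step 1: reproduce the plan's figure.** Unadjusted two-sample t-test, equal arms.
- A difference of 3.5 with SD 4 is 3.5/4 = 0.875 SD. This needs 21.5, so 22 per arm, which matches A4.2.
- An effect size of exactly 0.9 needs 20.4, so 21 per arm.
- With 22 per arm, power is 0.83 at 0.9 SD and 0.81 at 0.875 SD. The effect detectable with 80% power is 0.865 SD, or 0.865 × 4 = 3.46 ml/kg/min.

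So 22 per arm does support the claim, provided that 22 is the number analysed.

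**Step 2: dropout rates available in the document.**
- Phase 2, implied by A4.1: 1 − 44/60 = 26.7%.
- Phase 1: 1 − 48/60 = 20%. A4.1 describes Phase 2 dropout as higher, so this is a mild assumption for Phase 2.

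**Step 3: completers if 44 are randomised** (number randomised × (1 − dropout)).
- At 26.7%: 44 × 44/60 = 32.3, about 16 per arm.
- At 20%: 44 × 0.80 = 35.2, or 17.6 per arm.

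**Step 4: power and detectable effect on A4.2's basis.**

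| Completers per arm | Power at 0.9 SD | Power at 3.5 ml/kg/min | Effect detectable with 80% power |
|---|---|---|---|
| 22 (A4.2) | 0.83 | 0.81 | 0.865 SD (3.5 ml/kg/min) |
| 17.6 (20% dropout) | 0.74 | 0.71 | 0.97 SD (3.9 ml/kg/min) |
| 16 (26.7% dropout) | 0.69 | 0.67 | 1.02 SD (4.1 ml/kg/min) |

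**Step 5: the number that restores A4.1.** 44 / (44/60) = 60, which is the recruitment figure already in A4.1.

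**Step 6: Form A.** Recruits in both phases: 60 + 60 = 120. Completers in both phases: 48 + 44 = 92. The declared 104 equals neither; it is 60 + 44.

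**The case against.** **Recruited is not randomised.** A4.1 says that 60 are recruited and gives no number randomised, and A4.3 allocates only after consent and baseline measurements. One could therefore read the plan as 60 recruited, 16 lost before allocation and 44 randomised. It is right that A4.1 should not be described as randomising 60. The reading does not repair the plan, however. A4.1 ties the dropout to the community-based phase itself and counts completers by arm, and Phase 1 has 60 both recruited and randomised. Even if all 16 losses came before allocation, nothing would remain for dropout over the 26 weeks.

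**The power loss is conditional.** The document states no dropout rate for a randomised cohort of 44, so the 16 to 17.6 per arm rests on an assumed range. The figures are also for an unadjusted comparison, whereas A5.2 plans ANCOVA with baseline as covariate, and the SD of 4 describes VO2max itself rather than its change. If ANCOVA reduces that SD by √(1 − r²), where r is an assumed correlation between baseline and follow-up, power for 3.5 ml/kg/min with 16 per arm is about 0.71 at r = 0.3, 0.79 at 0.5, 0.85 at 0.6 and 0.92 at 0.7. This stands: the real loss could be small or nil. But A4.2 claims no gain from adjustment, and its 22 per group reproduces without one.

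**Compensation coverage.** A reader might infer from Form A that 16 participants would fall outside accident-compensation cover. The documents do not support that. The form serves to show that the research is not principally for a manufacturer's benefit, and nothing in it limits cover to the declared number.

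**F2.1 is a recruitment aim.** The 50% target holds with either denominator. Only the count of 22 of 44 needs to follow the corrected number.

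**Conclusion.** The contradiction is real. A4.1 treats 44 as completers, Appendix 1 treats it as those randomised, and no reading of Appendix 1 gives 22 completers per arm without zero dropout. If 44 are randomised and dropout lies between 20% and 26.7%, about 32 to 35 people complete. On A4.2's unadjusted basis with SD 4, power at an effect size of 0.9 is then about 69–74%, against 83% with 22 per arm, and the detectable effect rises from 0.865 SD to about 0.97–1.02 SD.

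It would go too far to say that the trial will be underpowered. That depends on whether Appendix 1 or A4.1 is followed, on the dropout that occurs, and on the precision gained from ANCOVA, for which the protocol gives no correlation. The Form A figure is an inconsistency in the declared study size and no more.

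**What to change.** Reconcile A4.1, F2.1, Form A and Appendix 1 to one Phase 2 enrolment number, and state separately how many are randomised and how many are expected to complete.

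- **If 60 is intended:** in Appendix 1, state that 60 new participants are randomised, 30 per group, with 44 expected to complete, 22 per group. Change Form A to 120 and F2.1 to 30 of 60 recruited. A4.2 can stay. This is a change of wording only, since A4.1 already plans for 60.
- **If 44 randomised is intended:** restate A4.1 with about 32 to 35 completers and the dropout rate assumed, and restate A4.2 with a detectable effect of about 0.97–1.02 SD (3.9–4.1 ml/kg/min). If the authors want to rely on ANCOVA to hold the smaller effect, A4.2 should give the correlation assumed and its source.

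The documents do not settle which number was resourced. Three places carry 44 and one carries 60. If budgets were set on 44, the first option means 16 more people (60 − 44), each with the seven research visits listed in B1. The choice should be made before Phase 2 enrolment begins.

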#### A5. Statistical method

| A5.1 Is the method of analysis quantitative? | | | X | Yes |  | No |
| --- | --- | --- | --- | --- | --- | --- |
|  | | | | | | |
| Or qualitative? | | |  | Yes | X | No |
|  | | | | | | |
| If the method of analysis is **wholly qualitative**, go to question A5.4. If the method of analysis is **wholly or partly quantitative**, complete the following: | | | | | | |
|  | | | | | | |
| A5.2 Describe the statistical method that will be used to analyse the data. | | | | | | |
|  | Initial data analysis will be conducted by [name] and colleagues using the Statistical Package for the Social Sciences (SPSS) software programme. Final data analysis will be undertaken under the supervision of Associate [name], medical biostatistician. For both studies changes in continuous outcome measures (e.g. VO2max, BMI, etc) will be compared between groups using ANCOVA. These models will utilise the stratification variable, gender, as a factor and the baseline measure as a covariate. The appropriateness of these parametric analyses will be confirmed by visual inspection of the residual plots. If these do not confirm normality, data maybe transformed prior to analyses and if this does not remedy problems then non-parametric analyses will be undertaken. A two-tailed p value of <0.05 will be taken to indicate statistical significance.  The primary outcome measure is change in VO2max.  The secondary outcome measures are changes in: BMI, waist circumference, blood pressure, insulin sensitivity (HOMA) and lipids.  Tertiary outcome measures are changes in: % body fat as measured by bioimpedance, Quality of Life, hs CRP.  Samples will also be collected for an exploratory study measuring changes in a novel marker of muscular ‘fitness’, namely monocyte mitochondrial load. | | | | | |
|  | | | | | | |
| A5.3 Has specialist statistical advice been obtained about this study? | | | X | Yes |  | No |
|  | | | | | | |
| If **yes**, from whom? (A brief statistical report should be included if appropriate.) | | Associate [name], University of Otago. | | | | |
|  | | | | | | |
| A5.4 If the method of analysis is **wholly or partly qualitative**, specify the method. Why is this method appropriate? If interviews are to be used, include the general areas around which they will be based and a copy of the interview guide, if one is to be used. Copies of any questionnaires that will be used must be included. | | | | | | |
|  | Not applicable | | | | | |

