**Phase 2.**

The subjects will be randomly selected to one of 2 groups (Low intensity control group and High-intensity intervention group). The exercise prescription for these two groups will be based on the outcomes from phase 1 of the study and will be for 26 weeks rather than twelve weeks. The measurement of V02 max, fasting blood samples, questionnaires and anthropomorphic measurements will be as for Phase 1, but undertaken at 0, 13 and 26 weeks. Mitochondrial depletion studies will not be undertaken for Phase 2 (ie they will be done for Phase 1 only). The only location that will change is the location for the exercise prescription, which will now be near the subjects’ own home ie around the Aranui or Halswell area.

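### Phase 2 uses two training venues, but the protocol does not say that both arms run at each, and venue enters neither the stratification nor the ANCOVA

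*Protocol*

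**What the plan says.** **Delivery.** The Phase 2 paragraph of Appendix 1 randomises participants into two groups of 22. It then says: "Once a week each exercise group will come together at a local venue (Halswell Health Medical Centre or the Whanau Tautoko Charitable Trust"). The other two weekly sessions are held wherever the participant chooses, and B1 confirms that one session a week is supervised and two are not. The closing Phase 2 paragraph of Appendix 1 says that the exercise location will now be close to where participants live, "ie around the Aranui or Halswell area".

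**Randomisation (A4.3).** "For both studies it is important to achieve a balance in gender and this will be achieved by stratified randomisation". No other stratification factor is named.

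**Analysis (A5.2, both phases).** "These models will utilise the stratification variable, gender, as a factor and the baseline measure as a covariate". Venue is not mentioned.

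**Phase 1, for comparison.** All supervised sessions are in Hagley Park, so venue could not differ between arms.

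**Size (A4.1 and A4.2).** "60 participants will be recruited, anticipating that 44 participants will complete the study (22 in each arm"). "A sample size of 22 per group in the second study will enable effect sizes >0.9 to be detected as statistically significant".

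**The concern.** The gender-only rule is carried from a phase with one training site into a phase with two. Two separate questions follow.

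The first is logistic: does each arm train at both venues? In the Phase 2 paragraph the word for the two randomised arms and the word for the people who meet at a venue are nearly the same, and the venues are joined by "or". One venue per arm is therefore a possible reading. Any difference between sites in attendance or support would then be counted as an effect of exercise intensity in the effectiveness comparison.

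The second is statistical and arises even if both arms run at both venues. Venue is then a known baseline factor that may relate to the response, yet it is neither balanced by design nor adjusted for.

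**Working it through.** **Inputs from the protocol.** 22 completers per arm, two-sided alpha 0.05 and 80% power (A4.2); SD 4, from "Assuming an untrained VO2 max of 30 ± 4ml/kg/min", used here as the SD of change; target difference about 3.5 ml/kg/min.

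**Assumptions, not in the protocol.** Completers split 22:22 between venues; venue effect *v* on change in VO2max between 0 and 3.5 ml/kg/min. Gender and baseline are left out of the calculation.

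**1. The plan's own figure.** For the two-sample t-test with n = 22 per arm, the non-centrality is d × √(n/2), on 42 df.
- d = 3.5/4 = 0.875: power 80.9%.
- d = 0.9 (a difference of 0.9 × 4 = 3.6 ml/kg/min): power 83.0%.

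So 22 per arm is adequate as stated. Recruitment also agrees: the loss is 16/60 = 26.7%, and 44/(1 − 0.267) = 60.

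**2. Reading by home area, both arms at both venues.** Venue is fixed before allocation, so any imbalance is due to chance. The number from one venue who fall in one arm is hypergeometric (44 people, 22 at the venue, 22 in the arm):

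| Split within a venue | Probability (either direction) | Difference between arms in venue share |
|---|---|---|
| 14:8 or worse | 0.131 | 6/22 = 0.27 |
| 15:7 or worse | 0.034 | 8/22 = 0.36 |
| 16:6 or worse | 0.006 | 10/22 = 0.45 |

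The shift in the contrast in a given trial is *v* × the difference in share. For *v* = 2 and a 14:8 split it is 2 × 0.27 = 0.55 ml/kg/min. The standard error is 4 × √(2/22) = 1.21, so the shift is about 0.45 SE, in either direction. Type I error conditional on that split is about 7%.

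Over all randomisations the shifts cancel. Simulation (4,000 runs per scenario, true difference 3.6 for power, allocation not stratified by venue) gave:

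| Assumed *v* (ml/kg/min) | Type I error without venue term | Power without venue term | Power with venue term |
|---|---|---|---|
| 0 | 5.0% | 82.9% | 81.9% |
| 1 | 4.7% | 83.2% | 82.4% |
| 2 | 4.6% | 80.9% | 82.4% |
| 3.5 | 5.2% | 76.3% | 82.1% |

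A closed form confirms the third column. With equal venues, an omitted venue effect raises the SD to √(16 + *v*²/4). For *v* = 3.5 this is √(16 + 3.06) = 4.37, so d = 3.6/4.37 = 0.82 and power is 76%. For *v* = 2 it is √17 = 4.12, so d = 0.87 and power is 81%.

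**3. Literal reading, one venue per arm.** The whole of *v* enters the contrast. With no true difference between arms, the rejection rate is the power of the t-test at *v*/4: 6.9%, 12.8%, 36.7% and 80.9% for *v* = 0.5, 1, 2 and 3.5. A venue column in the model would be identical to the arm column, so adjustment is impossible.

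**The case against.** The strongest case is that this is a drafting ambiguity with an obvious resolution. One venue per arm would make the randomisation decide where people train, which conflicts with training close to home. Phase 1 uses the language of exercise groups for training subgroups of about six, and the Phase 2 sentence may do the same. Two of three weekly sessions are held elsewhere, which makes a large venue effect less likely. The venue effect is itself assumed. A covariate such as venue could be added in a statistical analysis plan, and Appendix 1 expects Phase 1 results to refine the Phase 2 procedures.

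Most of this stands. It makes the home-area reading the likelier one, where type I error stays near 5% and the loss of power is visible only for a large venue effect. It does not settle the matter. No sentence says that both arms run at both venues. Where each arm trains and which factors are stratified are design decisions that an analysis plan written later cannot recover.

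Some stronger inferences are not supported:
- **That the two sites are very different, or have different ethnic mixes.** D1 names the Trust as the main initial recruitment route, and F2.1 aims for 50% Maori participation across the phase. Neither says who trains where.
- **That instructors differ by site or arm.** Appendix 1 describes one pool for both.
- **That modelling gender alone causes confounding of arm with venue.** It neither causes nor cures it. Only running both arms at each site prevents it.

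**Conclusion.** The point holds as a gap in the design description together with a cheap gain in efficiency. It does not show that the Phase 2 comparison is confounded.

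On the likelier reading there is no systematic bias. The cost is a chance of about 0.13 of a 14:8 or worse split, and a power loss of about 6 percentage points (76% against 82%) at an assumed venue effect as large as the target difference. At 2 ml/kg/min the loss is between one and two points, and at 0 or 1 there is none. These figures rest on an even venue split and SD 4 for change.

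On the literal reading the comparison could not be interpreted as an effect of intensity. The protocol does not establish that reading, but it leaves it open, and the damage could not be repaired after the fact. The stated sample size is sound on either reading.

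**What to change.** 1. In the Phase 2 paragraph of Appendix 1, state that both arms hold weekly supervised sessions at each venue, and say whether the groups that meet there are arms or training subgroups within arms.
2. Assign each participant's venue by home area before randomisation.
3. In A4.3, stratify Phase 2 randomisation by venue and gender (four strata, with small blocks).
4. In A5.2, add venue as a factor to the Phase 2 ANCOVA.

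Steps 2 to 4 work only if step 1 holds. Rostering instructors across arms within each venue is an optional operational precaution.

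**Cost.** One degree of freedom, about one percentage point of power if venue has no effect (82% against 83%), and possibly one extra weekly slot at a venue that would otherwise host a single arm. The numbers recruited and analysed do not change.
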